### Sample size determination

Sample size is calculated using Power and Sample Size Calculation software version 3.1.2 [84], based on the findings of a randomised controlled trial evaluating the effects of a web-based self-management intervention for adults with chronic conditions on patient activation scores, measured by the PAM-13 questionnaire [48]. In the intervention group, the mean patient activation score at baseline was 65.33, and the mean score after the intervention was 71.30 (mean difference, 5.97 ± 9.70; t57 = 4.683; *P* < 0.001) [48]. In the control group, the mean patient activation score at baseline was 66.89, and the mean score at the end of the study period was 68.93 (mean difference, 2.04 ± 10.01; t67 = 1.677; *P* = 0.10) [48]. Therefore, the mean difference between the two groups was 3.93.

Based on this assumption, a sample size of 97 patients per group is sufficient to detect mean difference of δ = 3.93 in the patient activation score between the two groups, with a standard deviation of σ = 9.70 using a two-tailed *t* test of difference between means with 80% power (power = 0.8), 5% level of significance (α = 0.05), and sample size ratio of 1:1 between the two groups (m = 1). After considering a drop-out rate of 20%, the sample size required is 116 patients per group, giving a total of 232 patients to be recruited for this study.

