**Methods:**

A pilot randomised controlled trial will be conducted in a university primary care clinic. A total of 232 patients aged 18–60 years with MetS will be recruited; 116 will be randomised to receive the EMPOWER-SUSTAIN intervention for 6 months, and another 116 patients will continue with usual care. The EMPOWER-SUSTAIN intervention is a multifaceted chronic disease management strategy based on the Chronic Care Model and persuasive technology theory. It consists of training primary care physicians, nurses and patients to use the EMPOWER-SUSTAIN web-based self-management mobile app, strengthening the patient–physician relationship and reinforcing the use of relevant clinical practice guidelines to guide management and prescribing. The primary outcome is the mean change in patient activation score using the Patient Activation Measure short form Malay version (PAM-13-M) questionnaire. The secondary outcomes include the changes in waist circumference, body mass index, blood pressure, patient physical activity level, eating behaviour, perception of chronic illness care, satisfaction with patient–physician interaction, and perceived absolute 10-year cardiovascular disease risk. Feasibility of implementing the intervention will be evaluated. This includes acceptability of the intervention, estimating the likely rate of participant recruitment and retention, appropriateness of the outcome measures, calculation of sample size, and the intervention’s potential effectiveness.

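### The drop-out allowance multiplies 97 by 1.2 instead of dividing by 0.8, so 116 per group leaves about 93 after 20% loss and power is about 78%, not 80%

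*Protocol article*

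**What the plan says.** The sample size rests on a published randomised trial of a web-based self-management intervention that also used PAM-13. The mean change was 5.97 (SD 9.70) in its intervention arm; for its control arm the article reports "mean difference, 2.04 ± 10.01". From these it concludes: "Therefore, the mean difference between the two groups was 3.93". It then sizes the trial "using a two-tailed *t* test of difference between means", "with a standard deviation of σ = 9.70", at 80% power, 5% significance and 1:1 allocation, which gives 97 per group. The allowance for losses follows: "After considering a drop-out rate of 20%, the sample size required is 116 patients per group, giving a total of 232 patients".

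The abstract repeats the total: "A total of 232 patients aged 18–60 years with MetS will be recruited". Under Monitoring the intervention, the article adds that patients who are lost or withdraw are not replaced, and that patients who miss the app-use and follow-up requirements count as lost.

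**The concern.** A drop-out rate is a fraction of those recruited. If a fraction d is lost, the number to recruit is the evaluable number divided by (1 − d). Multiplying by (1 + d) always falls short; at 20% it retains 1.2 × 0.8 = 0.96 of the target. The stated 116 looks like the product of that shortcut.

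If so, the article makes three statements that do not fit together: 116 recruited per group, 20% drop-out, and the 80% power attached to 97 evaluable patients. A reader who takes the paragraph at face value would expect 80% power after the planned losses.

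**Working it through.** **Inputs**, all from Sample size determination: difference δ = 5.97 − 2.04 = 3.93; σ = 9.70; two-sided α = 0.05; power 0.80; ratio 1:1; drop-out d = 0.20.

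**1. Reproducing 97.** The normal approximation is n = 2(z₀.₉₇₅ + z₀.₈₀)² σ²/δ² = 2 × (1.960 + 0.842)² × (9.70/3.93)² ≈ 95.6, so 96. The exact noncentral-t solution is 96.6, so 97. Exact power at 97 per group is 80.2%. The evaluable number is right for the stated inputs.

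**2. Reproducing 116.** 97 × 1.2 = 116.4, which gives 116 when rounded down. Division gives 97/(1 − 0.20) = 121.25, so 122 per group and 244 in total. Only the multiplication matches the article.

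**3. What 116 delivers at 20% drop-out.** 116 × 0.8 = 92.8 per group, about 4 short of 97. Exact-t power at 92.8 per group with σ = 9.70 is 78.4% (normal approximation 78.8%).

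**4. Drop-out that 116 does cover.** 1 − 97/116 = 19/116 = 16.4%. With no drop-out at all, power at 116 per group is 86.7%.

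**5. Sensitivity to the standard deviation.** The quoted t statistics have 57 and 67 degrees of freedom, so the source arms had 58 and 68 patients. Both quoted SDs behave as SDs of change: 5.97/(9.70/√58) = 4.69 (quoted 4.683) and 2.04/(10.01/√68) = 1.68 (quoted 1.677). The pooled value is √[(57 × 9.70² + 67 × 10.01²)/124] = 9.87.

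| SD | Power at 97 per group | Power at 92.8 per group |
|---|---|---|
| 9.70 (plan) | 80.2% | 78.4% |
| 9.87 (pooled) | 78.8% | 77.0% |

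The first row uses only the plan's own inputs and carries the point. The second row is a sensitivity figure.

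**The case against.** The strongest reply is that this hardly matters. The loss is 1.6 points of nominal power, while the planning effect itself is very uncertain. From the quoted figures, the standard error of the 3.93 difference is √(9.70²/58 + 10.01²/68) ≈ 1.76, a 95% interval of roughly 0.4 to 7.4. The trial is a pilot whose stated purpose is feasibility and potential effectiveness, and no feasibility conclusion turns on 78% against 80%. This stands, and it limits the importance of the point. It does not make the stated numbers consistent.

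Intention-to-treat analysis might be thought to close the gap. It does not: inflating for drop-out already assumes that drop-outs do not count towards the 97, and outcomes are taken only at baseline and 6 months, so a patient lost in between has no follow-up value.

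Three stronger readings are tempting and are not supported:

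- *That the trial fails to deliver 80% power.* The article attaches 80% to 97 evaluable patients, which is correct. The shortfall arises only if drop-out exceeds about 16%.
- *That using 9.70 is a second arithmetic error.* The article shows both SDs and says which one it used. 9.70 is the smaller of the two and so optimistic, but the gap to 9.87 is under 2%. The 95% interval for the 9.70 estimate, from 58 patients, is about 8.2 to 11.9, so the choice lies well within the uncertainty of the source.
- *That the error will pass into the definitive trial.* The article lists sample size calculation among the things that the pilot will evaluate, but nowhere says that the 1.2 multiplier will be reused.

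**Conclusion.** The point holds for the inflation step alone. With 116 recruited per group, 20% drop-out in each arm and no replacement, about 93 per group remain and power is about 78% at δ = 3.93 and σ = 9.70. Retaining 97 would take 122 per group, 6 more in each arm. The conclusion rests on the article's own inputs, on a two-sample comparison of changes, and on drop-outs contributing nothing to that comparison. The effect is minor: a misstated planning figure that should be corrected, not a flaw that threatens the pilot.

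**What to change.** Keep 232 patients and restate the last sentence of Sample size determination, for example: *Recruiting 116 patients per group (232 in total) gives about 78% power after 20% drop-out, assuming an SD of 9.70; 80% power is kept for drop-out up to about 16%.* Optionally add: *With the pooled SD of 9.87 from the two source arms, power after 20% drop-out is about 77%.* The total in the abstract can stay as it is.

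This costs wording only, plus a slightly less favourable power statement. If the trial team prefers to keep both 80% power and a 20% allowance at SD 9.70, the number becomes 122 per group, 244 in total, which is 12 more patients.

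Any later sample-size calculation should use n/(1 − d) for losses.

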### Randomisation

Randomisation of patients to either the EMPOWER-SUSTAIN Self-Management e-Health Intervention (I) or usual care (C) will be done using randomised block design by a research assistant. Random allocation will be done in order to keep the sizes of the groups similar. In this study, the block randomisation size will be four times the number of treatment arms (i.e., block size of 2 by 2). With two treatment arms of the EMPOWER-SUSTAIN Self-Management e-Health Intervention (I) or usual care (C), the possible treatment allocations within each block [85] will be as follows: IICC, ICIC, ICCI, CCII, CICI, CIIC. A research assistant will generate the allocation sequence, enrol the participants and assign the patients to the intervention or control arms according the sequence. The generated sequence will be placed in sealed envelopes to ensure that it is concealed from the PCPs until the intervention is assigned. Blinding is not possible, owing to the complexity of the intervention.

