### Trial design

This is a pilot randomised controlled trial with parallel group design (i.e., intervention vs. control [usual care] with an allocation ratio of 1:1). The overall duration of the study is 1 year, and the duration of the intervention is 6 months. Blinding is not possible, owing to the nature and complexity of the intervention.

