### Trial status

The development of the EMPOWER-SUSTAIN self-management mobile app is completed. However, due to the Covid-19 pandemic, we are unable to start participant screening and recruitment in March 2020 as previously planned. This study is expected to be delayed by 6 months. We hope to commence participant screening and recruitment in September 2020. The expected date of completion of patient recruitment is October 2020. Baseline data collection is planned to start in December 2020. The intervention is planned to be delivered for 6 months from January to June 2021. The outcome data will be collected in July to August 2021. The expected date of completion of this pilot trial is 31 December 2021.

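### Allocation is not concealed from the role that enrols: a research assistant generates the sequence, enrols and assigns, and the envelopes hide it only from the physicians

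*Protocol article*

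**What the plan says.** All of the key statements are in the Randomisation section of the protocol article.

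- **Roles:** "A research assistant will generate the allocation sequence, enrol the participants and assign the patients to the intervention or control arms according the sequence".
- **Concealment:** "The generated sequence will be placed in sealed envelopes to ensure that it is concealed from the PCPs until the intervention is assigned". No one other than the PCPs is named as kept from the sequence.
- **Block size:** "the block randomisation size will be four times the number of treatment arms (i.e., block size of 2 by 2", followed by the possible allocations within a block: "IICC, ICIC, ICCI, CCII, CICI, CIIC".
- **Blinding:** "Blinding is not possible, owing to the complexity of the intervention".

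Elsewhere, Trial design gives a parallel-group comparison "with an allocation ratio of 1:1", and Sample size determination sets the number, "giving a total of 232 patients to be recruited for this study". Patient recruitment has consecutive attenders approached and the investigators screening them for eligibility. The primary outcome is the change in the PAM-13-M score, a self-administered questionnaire. Trial status shows that recruitment had not begun.

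**The concern.** Allocation concealment protects the comparison up to the moment a patient is irrevocably in the trial. It has to work against whoever enrols. Here the same role writes the list and enrols, and an envelope cannot hide a list from its author. Keeping the PCPs unaware does not help if the person placing patients into the next slot knows what that slot holds.

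The risk is selection: a patient thought likely to do well with the app could be enrolled earlier or later, or not at all, depending on the next arm. Nothing in the text suggests this is intended, but nothing described prevents it. With no blinding and a primary outcome that patients report on their own knowledge, skills and confidence, such selection would act on a trait close to what is measured. The Study setting section wants the pilot to support safe assumptions about effect size for a definitive trial, and Feasibility outcomes lists the randomisation method among the things being evaluated. A distorted estimate would carry forward into that trial.

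The small fixed block adds a second, lesser route. Staff who do not hold the list but see assignments accumulate can work out some of the later ones.

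**Working it through.** **Who knows what, as written.** This part needs no arithmetic.

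| Task or safeguard | Who, according to the Randomisation section |
|---|---|
| Generates the sequence | a research assistant |
| Enrols participants | a research assistant |
| Assigns to arm | a research assistant |
| Sequence concealed from | the PCPs |

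The first three rows name the same role, and the fourth does not cover it. If one person fills the role, that person knows every assignment in advance, whatever the block size.

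**Block size.** Inputs are two arms, 1:1 allocation and the six listed sequences.

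- A balanced block of 4 has C(4,2) = 6 orderings. This reproduces the six sequences listed, each of length 4.
- Four times the number of arms is 4 × 2 = 8. A balanced block of 8 has C(8,4) = 70 orderings, which does not match the list.
- The 2-by-2 description gives 2 × 2 = 4, which does match.

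So the list and the bracketed description agree on 4, and the verbal rule (8) contradicts them. With 232 patients there are 232/4 = 58 complete blocks.

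**Predictability of a fixed block of 4.** Take a person who does not hold the list, sees every earlier assignment in order and knows that the block size is 4. The best strategy is to guess the arm with more places left.

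| Position in block | Chance that the assignment is certain | Chance of a correct guess |
|---|---|---|
| 1 | 0 | 1/2 |
| 2 | 0 | 2/3 |
| 3 | 1/3 (first two were the same arm) | 1/3 × 1 + 2/3 × 1/2 = 2/3 |
| 4 | 1 | 1 |
| Sum | 1.333 | 2.833 |

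- Share certain: 1.333/4 = 33.3%, or 58 × 1.333 ≈ 77 of 232 assignments.
- Share guessed correctly: 2.833/4 = 70.8%, or 58 × 2.833 ≈ 164 of 232, against 116 of 232 (50%) by chance.

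**Comparison with a fixed block of 8.** Enumerating the 70 orderings in the same way gives 1.6/8 = 20.0% certain (29 × 1.6 ≈ 46 of 232) and 5.329/8 = 66.6% guessed correctly (29 × 5.329 ≈ 155 of 232). A longer fixed block reduces predictability only modestly, so varying and not disclosing the size is preferable to simply lengthening it.

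**The case against.** Several points on the other side are fair.

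- **The research assistant is not the one who judges eligibility.** A reader might infer that this role can bend the entry criteria. The text does not support that. The investigators interview and screen consecutive attenders, and the web-skills criterion is the patient's own perception. What remains is influence over who is enrolled and in what order.
- **Timing of baseline.** Trial status ends recruitment in October 2020 and then says "Baseline data collection is planned to start in December 2020". A reader might infer that patients answer the baseline questionnaires already knowing their arm. The documents do not establish this. Delivery starts in January 2021, so allocation after baseline fits the calendar, and the flow diagram and schedule of assessments (Figures 1 and 4) are not available here. This is not part of the finding.
- **The percentages are conditional.** They do not measure the main defect, because block size is irrelevant to someone who wrote the list. If assignments are made only after recruitment closes, which the calendar permits, earlier assignments could not guide recruitment.
- **Possibly more than one person.** The wording could cover different assistants. However, it names one role for all three tasks and states no separation.
- **Journal format.** Envelope numbering, opacity and list custody are details that an article may leave to the full protocol, and their absence is not criticised. The combination of roles is different, because the article states it outright.
- **Baseline adjustment.** It would be too strong to say that analysis can do nothing. PAM-13-M is measured at baseline in both arms, so imbalance in measured activation would be visible and partly addressed. Unmeasured motivation would not.
- **Pilot status.** Randomisation is itself under evaluation, which tempers severity. It does not excuse a gap that is known before recruitment starts.

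**Conclusion.** The concern holds for the combination of roles. On the article's own wording, the sequence is concealed from the PCPs but not from the role that enrols and assigns. The size of any resulting bias cannot be calculated from the documents. It depends on whether the role is filled by one person, whether the list exists before enrolment, and whether that knowledge is acted upon. What can be said is that, with one person in the role and the list made first, every assignment is known in advance to the enroller.

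The fixed block of 4 is secondary. The 33% certain and 71% guessable figures are an upper bound, for a person without the list who sees all earlier assignments and knows the block size.

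The block-size sentence is an internal contradiction (8 against 4). The listed sequences settle the intended size as 4, so it is a matter of wording and does not by itself change conduct.

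**What to change.** 1. Assign generation and custody of the sequence to an existing team member who does not screen, enrol or assign patients. State in the Randomisation section that the sequence is concealed from everyone who recruits, not only from the PCPs.
2. Preferably generate the list with randomly varying block sizes (for example 4 and 8) that are not disclosed to recruiting staff.
3. Have the list holder prepare sequentially numbered, opaque, sealed envelopes. The research assistant opens the next one only after consent, confirmed eligibility and completed baseline measures.
4. Correct the block-size sentence so that the stated rule and any listed sequences agree. If varying blocks are adopted, remove the list of six sequences.

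**Cost.** One task moves between existing staff and a few sentences change. Fixed blocks of 4 divide 232 exactly, whereas varying blocks may leave the last block incomplete. With a largest block of 8, the final difference between arms is at most 8/2 = 4 patients, which is negligible against 116 per arm. According to Trial status recruitment had not started, so the change could be made before the first allocation.

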### Data management

Each CRF will be given a unique identifier. Data collected using the CRF and all the questionnaires will be checked by a research assistant to ensure completeness. If any missing data are found, the patients will be contacted again via telephone. Double data entry into the IBM SPSS Statistics version 24 software (IBM, Armonk, NY, USA) will be conducted, and data cleaning will be done to manage outliers, missing values, and inconsistencies. The clean datasets for baseline and outcome will be used for analysis. Data will be stored in a secure database at the Institute of Pathology, Laboratory and Forensic Medicine (I-PPerForM), Universiti Teknologi MARA (UiTM).

### Statistical analysis

The analysis will be conducted using IBM SPSS Statistics version 24 software.

#### Descriptive analysis

Frequency distribution, a measure of central tendency and dispersion, will be produced. For the continuous data, it will be presented by mean and standard deviation or median based on the normality of the data. For the categorical data, it will be presented by absolute number and the corresponding percentage.

#### Effectiveness analysis

ITT analysis will be applied to measure the potential effectiveness of the EMPOWER-SUSTAIN Self-Management e-Health Intervention on the primary and secondary outcome measures based on the initial treatment assignment. Mixed model repeated measures analysis of variance will be carried out to evaluate the potential effectiveness (i.e., to compare the mean changes in patient activation, PA, diet, patients’ chronic illness care, and patient–physician interaction satisfaction scores) with regard to perceived absolute 10-year CVD risk within and between the intervention and control groups at baseline and 6-month follow-up.

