#### IPAQ-M

The IPAQ was developed to measure health-related PA in the English language [78] and was previously translated into the Malay language and validated in the Malaysian population [70]. The IPAQ-M short version comprises of 12 items, covering vigorous, moderate, walking, sitting and sleeping activities [70]. Patients are required to report the activities performed during the last 7 days and to include only activities that lasted 10 min or more per session. IPAQ will be scored according to its scoring protocol [79]. Continuous score will be expressed as metabolic equivalent task (MET) minutes per week: MET level × minutes of activity/day × days per week [79]. The scores will then be categorised into ‘low’, ‘moderate’ and ‘vigorous’ PA levels in accordance with the Malaysian CPG on Primary and Secondary Prevention of Cardiovascular Disease 2017 [64]. The IPAQ-M short version has acceptable validity for moderate, vigorous and total PA and was found to be reliable for assessing PA of Malay adults [70].

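### Physical activity in MET-minutes is compared as raw mean change with no provision for skew; a baseline-adjusted comparison with a pre-specified rank-based companion would be a cheap, minor improvement

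*Protocol article*

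**What the plan says.** The Effectiveness analysis section of the protocol article gives one method for the questionnaire outcomes: "Mixed model repeated measures analysis of variance will be carried out to evaluate the potential effectiveness". Its stated purpose is "to compare the mean changes in patient activation, PA, diet, patients’ chronic illness care, and patient–physician interaction satisfaction scores". PA is therefore named, and the quantity compared is a mean change. No transformation, rank method or other fallback is given. Outcomes are measured at baseline and at 6 months only (Outcome measures).

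The IPAQ-M section defines the PA measure: "Continuous score will be expressed as metabolic equivalent task (MET) minutes per week", obtained by multiplying MET level, minutes per day and days per week. Only sessions of at least 10 minutes count. The same section adds that "The scores will then be categorised into ‘low’, ‘moderate’ and ‘vigorous’ PA levels", and Secondary outcomes lists the endpoint as a change in PA level. Whether the score or the category is tested is thus not fully settled, although the word for scores in the Effectiveness analysis section points to the continuous one.

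Two other statements bear on large or non-normal values. For description, continuous data will be "presented by mean and standard deviation or median based on the normality of the data". For data handling, "data cleaning will be done to manage outliers, missing values, and inconsistencies", with no rule given.

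**The concern.** PA differs from the scores listed beside it. PAM-13 runs from 0 to 100, DEBQ-M subscale means and PACIC-M items from 1 to 5, and SKIP-11 from 11 to 55. MET-minutes per week is a product with a floor at zero, possible zeros for inactive patients and a wide range above. Such a product can be strongly right-skewed. If it is, the difference between two visits is governed by the few patients who report most.

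Two things would follow. The baseline table could show medians while the test compares means, so the description and the inference would concern different quantities. The estimated PA effect would also be imprecise and unstable. That matters somewhat because the Study setting section says the pilot should support safe assumptions about effect size for the definitive trial, and PA is one of the self-management behaviours in the objective.

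**Working it through.** **The plan's own figure.** The only sample size stated is for PAM-13: difference 3.93, SD 9.70, two-sided 5%, 80% power. The t-based calculation gives 96.6, so 97 per group (power 80.2%), which reproduces the plan. It says nothing about PA. Recruiting 116 per group with 20% drop-out leaves 116 × 0.8 = 92.8, so 93 per arm is used in steps 3 to 5.

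**Step 1: what the planned test is.** With two arms and two visits, the group-by-time test in a repeated-measures ANOVA is a two-sample t test on change, D = (6-month value) − (baseline value).

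**Step 2: why adjusting for baseline helps.** With equal variance σ² at both visits and correlation r, Var(D) = 2σ²(1 − r), whereas the residual variance after adjustment is σ²(1 − r²). The ratio is (1 + r)/2, which is below 1 whenever r < 1. For log-normal data with log-SD s and log-scale correlation 0.5, r = (exp(0.5s²) − 1)/(exp(s²) − 1). At s = 1.0 this is 0.649/1.718 = 0.38, so the variance ratio is 1.38/2 = 0.69.

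**Step 3: power by simulation.** Assumed, because the article gives no PA distribution: log-normal MET-minutes, log-scale correlation 0.5, true 40% increase, 93 per arm, two-sided 5%.

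| Setting | Analysis | log-SD 0.8 | 1.0 | 1.3 |
|---|---|---|---|---|
| No zeros | Planned mean change | 69% | 42% | 19% |
| | Mean, baseline-adjusted | 77% | 50% | 24% |
| | Rank, baseline-adjusted | 89% | 68% | 51% |
| 10% zeros per visit | Planned mean change | 56% | 34% | 16% |
| | Mean, baseline-adjusted | 66% | 44% | 21% |
| | Rank, baseline-adjusted | 66% | 48% | 33% |

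Repeat runs of 1,500 trials per cell differed from the no-zeros figures by at most 5 points. Type I error of the planned test was about 4% to 6%. The five most extreme of 93 patients in an arm carried 56% to 74% of the sum of squares of change. At log-SD 0.5 without zeros, all methods had about 99% power.

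**Step 4: a second design.** Here there were 97 per arm, with the effect set so that a log-scale analysis of change has 80% power, and log-scale correlation 0.3 to 0.7. The planned test lost about 1 to 6 points at log-SD 0.5, 17 to 26 at 1.0 and 38 to 47 at 1.5.

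**Step 5: does the advantage of ranks hold up?** Same base as step 3; order log-SD 0.8 / 1.0 / 1.3.

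- 10% zeros and scores capped at four times the median: baseline-adjusted mean 69/53/33%, rank 65/49/30%.
- 20% zeros, no cap: baseline-adjusted mean 55/34/17%, rank 45/31/19%.
- Benefit confined to 15% of treated patients (fourfold gain): planned test 53/34/15%, rank 34/29/19%.

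Adjusting for baseline beat the planned test in all the settings of step 3 where there was an effect. The further gain from ranks depends on zeros, caps and the shape of the benefit.

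**The case against.** The strongest reply is that the article gives no PA distribution, SD, proportion of zeros or expected effect, so any loss of power is assumed. This stands: the figures are conditional, and with mild skew little is lost. Minutes per day and days per week are finite, so the score is not literally unbounded. The article also states that "IPAQ will be scored according to its scoring protocol", and that protocol, which is not shown, may cap or truncate values.

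A reader might infer that the Descriptive analysis section contradicts the Effectiveness analysis section. It does not. The median rule is conditional, applies to presentation, names no variable and does not predict that any will be non-normal. What remains is an asymmetry: description has a provision for non-normal data and inference has none.

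A reader might also infer that extreme values would produce false PA findings, or that ranks should simply replace the ANOVA. The simulated type I error stays near 5%, which rules out the first. Step 5 of the working rules out the second. A mean difference with its SD is also useful for planning a larger trial, which a rank shift or odds ratio does not supply.

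Finally, handling of a skewed secondary score is often left to an analysis plan, and Feasibility outcomes makes the statistical methods something the pilot evaluates. This limits the importance of the point but does not remove it, because the article does state a method and names PA under it.

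**Conclusion.** The point holds as a minor one. The article commits PA to a comparison of raw mean changes, with no provision for skew in a score built as a zero-floored product. It also leaves slightly open whether the score or the category is analysed.

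If MET-minutes are skewed at log-SD 0.8 to 1.3 and the true increase is 40%, the planned test has about 69% down to 19% power. Adjusting for baseline adds 5 to 8 points (77 − 69, 50 − 42, 24 − 19). Baseline-adjusted ranks add 20 to 32 points (89 − 69, 68 − 42, 51 − 19) when there are no zeros. The estimate would also rest on a few high reporters. All of this depends on the assumed distribution, correlation and effect.

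The documents do not support an internal contradiction, an unconditional loss of power, or inflated false positives. PA is an unpowered secondary outcome in a pilot, so the change is optional.

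**What to change.** In the Effectiveness analysis section, for IPAQ-M MET-minutes per week only:

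- State that the continuous score is the variable analysed.
- Compare the 6-month value between arms adjusted for the baseline value, instead of comparing raw change.
- Pre-specify a baseline-adjusted rank-based or proportional-odds analysis, to be reported alongside if the score is skewed, with medians and quartiles by arm.
- Report the baseline-adjusted mean difference in every case.
- Do not rely on log(x + 1): with 10% zeros its power was only 13% to 17% in the simulations.

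The cost is one or two sentences, written before outcome data are seen. The downside is that a rank shift or odds ratio is not a mean difference in MET-minutes. Its advantage also shrinks or reverses with many zeros, capped scores or benefit concentrated in few patients, which is why the adjusted mean difference should stay in the report.
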